**Fig. 2 Fig2:**
[figure not shown]
Proposed study timeline

## Conceptual framework

The study’s foundation rests on three key theoretical elements: the Basic Psychological Needs mini-theory within self-determination theory (SDT) [41], the biopsychosocial model [42], and Obesity-Related Behavioral Intervention Trials (ORBIT) model [43]. SDT asserts that autonomy, competence, and relatedness are essential for human motivation and well-being; the biopsychosocial model suggests that health and illness are shaped by biological, psychological, and social factors, underscoring the interconnected nature of these dimensions in comprehending human health and disease; meanwhile, ORBIT furnishes a structured approach for crafting and assessing behavioral interventions aimed at obesity, merging insights from health psychology, behavioral economics, and implementation science to optimize intervention efficacy and longevity. Each of these models guided the methodology development for the study’s three aims. Specifically, the Basic Psychological Needs mini-theory within SDT aids in predicting and examining outcome-influencing factors. The biopsychosocial model assists in describing and interpreting findings without directly predicting outcomes; and the study is guided by the systematic approach to intervention development and testing posited by the ORBIT model. Figure 3 provides an overview of the conceptual framework.

**Fig. 3 Fig3:**
[figure not shown]
Conceptual framework

### Aim 1 (needs assessment): assess adolescent females’ views on social media, physical activity, and factors impacting positive body image in the community

#### Aim 1: design

The study’s initial phase involves conducting a community-engaged research needs assessment (ORBIT Phase Ia) to identify the needs, goals, opportunities, and assets related to physical activity within the community. This phase aims to build on existing knowledge about the population-level effects of social media on psychosocial factors by gaining a detailed understanding of how these factors impact needs in rural populations. To achieve this, we will perform a comprehensive needs assessment focused on body image by surveying adolescents, parents, teachers, and school administrators. The survey will utilize a multilevel design that addresses individual, interpersonal, and community-level influences. The insights gained from this needs assessment will provide a foundational understanding of the interactions between social media, physical activity, and body satisfaction within the current school setting. Additionally, this assessment will inform future evaluations across additional school partners, enhancing the overall understanding of these dynamics in rural contexts.

AIM 1 will be conducted in one rural public school district in Indiana, including both the middle school and high school campuses. These schools serve students in grades 6 through 12 and are located in an under-resourced, predominantly White community where all students qualify for free and reduced-price meals. While we will not stratify recruitment by grade, we will aim to include students from each eligible grade level (6th–9th) to capture a range of developmental perspectives. Grade-level representation will be monitored during enrollment, and descriptive analyses will examine potential differences by grade to inform future iterations of the program. Recruitment is conducted in collaboration with school staff and includes multiple strategies to reach eligible students and parents. For students, in-school announcements and classroom visits by research staff are used to explain the study and distribute take-home flyers. Parents are informed through printed flyers sent home with students and direct communication facilitated by teachers or school administrators.

#### Aim 1: setting and sample

We have partnered with a rural Midwestern middle school and high school, serving predominantly White students from under-resourced communities. Given the district's high poverty rates, the entire student body qualifies for free and reduced meals. Our data collection plan involves surveying a sample of 50 rural students. This sample size has been selected to ensure feasibility while providing a sufficiently large cohort for outcomes to approximate normal distributions, in accordance with the central limit theorem [44, 45]. Our inclusion criteria for participants are as follows: students must be enrolled in middle or high school, specifically entering grades 6 through 9 in the spring 2024 semester. Additionally, participants must have parental consent and provide their own assent to participate in the survey. For AIM 1, the focus will be on exploring body image issues among female students within the rural youth sample. However, males will be included to allow for comparison between biological sexes, and to further guide intervention development for greater inclusion.

#### Aim 1: procedure

##### Youth survey

After securing parental consent, we will obtain assent from adolescents to ensure they fully understand the study’s purpose, requirements, and potential risks or benefits. Parental consent will be gathered remotely via an informed consent document distributed through Qualtrics survey software. Adolescent assent, along with survey administration, will be conducted in-person using Qualtrics. This approach is designed to enhance compliance and ensure that adolescents have a clear understanding of the study. The survey measures will include demographics, the Canadian Assessment of Physical Literacy (CAPL-2) [46], Basic Psychological Need Satisfaction and Frustration Scale (BPNSFS) [47, 48], Body Appreciation Scale (BAS-2) [49], and Body Shape Questionnaire (BSQ) [50, 51]. Additionally, youth-tailored questions related to social media use will be used. The survey also includes an item assessing parental control of social media, asking participants whether their parent or guardian monitors or limits their account access or screen time. This item will support exploratory analyses of how parental involvement relates to digital behavior and psychosocial outcomes. The survey is anticipated to take 15 min. See the *Measures* section for additional details and see Supplementary material 1 for the complete youth survey.

#### Aim 1: measures

##### Physical activity

The CAPL-2 will be used to assess self-reported physical activity behaviors and physical literacy in adolescents. The CAPL-2 assesses physical activity during physical education class, recess, lunch, right after school, evening, weekends, and spare time. The CAPL-2 is 22-items [52, 53]. Additionally, the CAPL-2 has been shown to be reliable for measuring physical literacy in adolescents [52]. Additionally, accelerometers (Axivity, AX3) will be used to objectively measure PA via daily steps. The AX3 has shown high validity in adolescent populations for measuring PA [54].

##### Psychological needs

Adolescents will rate the satisfaction of their psychological needs (i.e., autonomy, competence, relatedness) with the Basic Psychological Need Satisfaction and Frustration Scale (BPNSF). The BPNSFS consists of 24 items with scores on a 5-point Likert scale ranging from “strongly disagree” to “strongly agree.” Twelve items assessed satisfaction (with four questions each for autonomy, competence, and relatedness), and twelve items assessed frustration (with four questions each for autonomy, competence, and relatedness). The BPNSFS has demonstrated adequate internal consistency with Cronbach’s alpha coefficients of global basic psychological need satisfaction of 0.9, 0.80 for autonomy satisfaction, 0.81 for competence satisfaction, and 0.81 **for** relatedness satisfaction [47, 48].

##### Perceptions of body

The BSQ will be used to assess body satisfaction, comparison to others, and emotional aspects surrounding body weight. The BSQ has a Cronbach’s alpha value of.93 in female populations [55]. Additionally, the Body-Appreciation Scale (version 2) (BAS-2) will be used to assess body appreciation levels. The BAS-2 assesses body appreciation across a series of levels: *body competence, body acceptance, body respect,* and *body protection*. The BAS-2 has consistently exhibited robust internal consistency. A strong internal consistency is reflected in Cronbach’s alpha values surpassing 0.80 [49], a benchmark commonly recognized as indicative of the scale’s reliability.

##### Social media usage

Currently, there exists a lack of validated tools for quantifying social media usage. To achieve an objective assessment of social media usage, this study evaluated the daily average screen time and usage of social media applications. Data will be extracted directly from participants’ smartphones, utilizing their settings and screen time features. Participants will be asked to enter this data themselves to protect their personal information. Additionally, the Bergen Social Media Addiction Scale (BSMAS) [56] will be used to objectively measure levels of addiction to social media. The BSMAS is an 8-item questionnaire, derived from the Facebook Intrusion Questionnaire (FIQ), which measures Facebook addiction through behavioral addiction symptoms (e.g., withdrawal, relapse, reinstatement, and euphoria). However, the BSMAS assesses multiple social media platforms. The BSMAS has demonstrated reliable psychometric properties in adolescent females (α: 0.86) [57].

#### Aim 1: sample size

To determine the appropriate sample size for our study, we conducted power analyses using G*Power. For the initial linear regression model, a priori testing was conducted with a specified moderate effect size of 0.6, three predictors, and a significance level of 0.05. The analysis indicated that a sample size of 29 participants would be required to achieve adequate statistical power. A moderate effect size was deliberately selected to address a common limitation in feasibility studies, wherein inadequate sample sizes, low statistical power, and the potential for generating misleading results are prevalent [58]. A decision was made to avoid selecting a large effect size in order to maintain alignment with the intended scope of a feasibility study and to steer clear of encroaching upon the objectives more commonly associated with a randomized clinical trial [59]. Likewise, applying the same parameters to the logistic regression model, we also determined that a sample size of 29 participants would be necessary. Consequently, our research team aims to recruit a total of 30 or more participants for the implementation of AIM 1, ensuring that our study is appropriately powered to detect meaningful effects, and accounting for potential dropouts.

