MET	CAPL-2, Sex	To examine the effect of physical literacy (CAPL-2) and sex on physical activity levels (MET).
BSQ	CAPL-2, Sex	To determine the relationship between physical literacy and body image, adjusting for sex.
BAS-2	CAPL-2, Sex	To explore how physical literacy influences body appreciation, accounting for sex.

All models will use linear regression. For each model, we will report unstandardized beta coefficients, standard errors, 95% confidence intervals, and p-values. Variables will be checked for assumptions of linearity, normality, and multicollinearity prior to analysis

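### Aim 1 calls an effect size of 0.6 moderate, although in regression terms it is at or above large, so the claim of adequate power is not supported for a moderate effect

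*Protocol article*

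**What the plan says.** Under Aim 1: sample size, the protocol article describes a G*Power calculation for a linear regression: "a priori testing was conducted with a specified moderate effect size of 0.6, three predictors, and a significance level of 0.05". The result is 29. Power is described only as adequate, without a number. The section explains that a moderate effect was chosen on purpose, names low power as a common weakness of feasibility studies, and says a large effect was avoided.

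It then states that "applying the same parameters to the logistic regression model, we also determined that a sample size of 29 participants would be necessary" and that "our research team aims to recruit a total of 30 or more participants for the implementation of AIM 1". It presents this as giving suitable power for meaningful effects with room for dropout.

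Under Aim 1: setting and sample, the figure is different: "Our data collection plan involves surveying a sample of 50 rural students". That number is justified by feasibility and the central limit theorem, with no reference to the power calculation.

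Under Aim 1: data analysis, Table 1 lists ten regressions. Seven have two predictors and three have three. The table note says "All models will use linear regression", with coefficients, standard errors, 95% confidence intervals and p-values reported.

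**The concern.** An effect size of 0.6 in a multiple regression is not moderate on any of the usual regression scales. If 29 participants suffice only for a very strong relation, the section's two claims conflict: it cannot both avoid a large effect and have good power at 29 or 30.

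At stake is a stated property of Aim 1. A reader told that the survey is well powered for moderate relations would give its regression results more weight than the sample can carry. Those results are meant to inform the co-design topics of Aim 2.

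Two smaller faults sit in the same text: a sample size for a logistic model that is not among the planned analyses, and two Aim 1 sample figures with separate justifications and no link between them.

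**Working it through.** **Inputs from the protocol article.** Effect size 0.6, three predictors, alpha 0.05, N = 29, floor of 30 (Aim 1: sample size); N = 50 (Aim 1: setting and sample); two or three predictors per model (Table 1).

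**Assumptions, not in the document.** The effect size is f². Conventional benchmarks are f² = 0.15 for medium and 0.35 for large.

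**Formulas.** R² = f²/(1 + f²). For the overall test with u predictors, power is the probability that a noncentral F with u and N − u − 1 degrees of freedom and noncentrality λ = f²·N exceeds the central 5% critical value. For one coefficient, the numerator has 1 degree of freedom and f² is the partial f².

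**Step 1: reproduce the 29.** With f² = 0.6 and N = 29, λ = 0.6 × 29 = 17.4.
- Three predictors: critical F(3, 25) = 2.99, power 91.4%. The smallest N is 23, 28 or 33 for 80%, 90% or 95% power.
- Two predictors: critical F(2, 26) = 3.37, power 95.0%. The smallest N for 95% power is exactly 29.

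So 29 is a plausible output for f² = 0.6.

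**Step 2: what 0.6 means.**
- As f²: R² = 0.6/1.6 = 0.375.
- As f: f² = 0.6² = 0.36, R² = 0.36/1.36 = 0.26. Power at N = 29 with three predictors is then 71%.
- As a multiple correlation: R² = 0.6² = 0.36, f² = 0.36/0.64 = 0.5625.

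The conventional large value is R² = 0.35/1.35 = 0.26 and the medium value is 0.15/1.15 = 0.13. Every reading is at or above large.

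**Step 3: power for a medium effect, f² = 0.15.** λ = 0.15 × N, which is 4.35, 4.5 and 7.5 at N = 29, 30 and 50.

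| Test | N = 29 | N = 30 | N = 50 | N for 80% |
|---|---|---|---|---|
| Overall, three predictors | 33.6% | 34.9% | 58.2% | 77 |
| Overall, two predictors | 40.4% | 41.8% | 65.8% | 68 |
| One coefficient, three-predictor model, partial f² | 51.8% | 53.3% | 76.5% | 55 |

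**Step 4: effect detectable with 80% power.**
- At N = 30 with three predictors: overall f² = 0.42 (R² = 0.30).
- At N = 50: overall f² = 0.24 (R² = 0.19) with three predictors, 0.21 (R² = 0.17) with two, and partial f² = 0.16 for one coefficient in a three-predictor model.

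**Step 5: compare the sections.** The logistic sizing has no counterpart among the analyses, since the Table 1 note makes every model linear. A logistic sample size would also need an event probability and an odds ratio, and neither is given. The floor of 30 rests on the power calculation and the 50 on the central limit theorem. Neither section mentions the other.

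**The case against.** The best case for the plan has five parts.

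**The metric is not named, and the benchmarks are conventions from outside the document.** This is true, and the conclusion has to carry it as an assumption. But f², f and a multiple correlation all lead to the same place. As a standardised mean difference 0.6 might pass as moderate, but that is not an input for a three-predictor regression. It would need about 2 × (1.96 + 0.84)²/0.6² = 43.6, so 44 per group, for 80% power, which does not give 29.

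**The arithmetic is sound.** A reader might infer that 29 is a miscalculation, because it is not the exact minimum for three predictors at 80%, 90% or 95% power. The documents do not support that. No target power is stated, 29 gives 91% power with three predictors, and it is exactly the 95% size with two, as most Table 1 models have.

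**Thirty or more is a floor that 50 satisfies.** A reader might infer a flat contradiction, or that only one child is allowed for dropout. The wording does not bear this out: a minimum and a larger planned sample can coexist. What stands is that the two figures are not linked.

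**One-third power is the least favourable figure.** It applies to the overall test, three predictors and the floor of 29 to 30. Only three of the ten models have three predictors, the plan reports individual coefficients, and at 50 participants a single coefficient has 76% power. This stands, so the range must be shown. None of the figures reaches 80%.

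**Aim 1 is an exploratory needs assessment.** A reader might infer that null coefficients will be taken as proof of no relation. Nothing in the protocol says so. It speaks of exploring relationships and patterns, and already commits to 95% confidence intervals.

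**Conclusion.** The power statement is wrong as written and should be corrected, but the fault is not critical. An effect size of 0.6 is labelled moderate when, on every regression reading tried, it is at or above the conventional large value. The statement that a large effect was avoided is therefore also wrong, and the claim of suitable power for meaningful effects is not supported for a moderate effect. With f² = 0.15 and alpha 0.05, power lies between 34% and 53% at 29 to 30 participants and between 58% and 76% at 50, depending on the test.

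The R² of 0.375 rests on reading 0.6 as f²; the terms medium and large rest on the conventional values of 0.15 and 0.35.

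The logistic sizing matches no planned model, and the floor of 30 needs linking to the 50. The primary feasibility outcomes and the progression criteria belong to Aim 3, where the sample of 50 is justified separately by precision. None of them depends on an Aim 1 regression.

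**What to change.** In Aim 1: sample size, state 50 as the Aim 1 target, in line with Aim 1: setting and sample. Delete four things: the word moderate for 0.6, the statement that a large effect was avoided, the logistic sentence, and the claim of suitable power. Replace them with:

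*With 50 participants and alpha 0.05, 80% power is available for an overall f² of 0.24 (R² 0.19) with three predictors, 0.21 (R² 0.17) with two, and a partial f² of 0.16 for a single coefficient in a three-predictor model; regressions are exploratory and interpreted through 95% CIs.*

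The cost is wording only. No participants are added beyond the 50 already planned, and the confidence intervals are already to be reported. The stated power becomes less favourable.

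### Aim 1 sample size: the effect of 0.6 labelled moderate is above large on the likeliest regression scale, so about 30 participants (or 50) are not adequately powered for a moderate effect

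*Protocol article*

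**What the plan says.** Under the heading Aim 1: sample size, the protocol article reports that "we conducted power analyses using G*Power". For the linear regression, "a priori testing was conducted with a specified moderate effect size of 0.6, three predictors, and a significance level of 0.05". The result is that "a sample size of 29 participants would be required to achieve adequate statistical power". Power is not given as a number, and the scale of the 0.6 is not named.

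The section explains that a moderate effect was chosen because feasibility studies often have too few participants and too little power. It then adds, as a separate point, "A decision was made to avoid selecting a large effect size in order to maintain alignment with the intended scope of a feasibility study". The recruitment target is set at 30 or more, "ensuring that our study is appropriately powered to detect meaningful effects".

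Two other places bear on this. Aim 1: setting and sample plans a survey of 50 students, justified by feasibility and the central limit theorem rather than by power. Table 1, under Aim 1: data analysis, lists ten linear regressions, three with three predictors and seven with two. Coefficients, standard errors, confidence intervals and p-values are to be reported for each.

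**The concern.** In linear multiple regression, G*Power takes f-squared as its effect size. The usual benchmarks on that scale are 0.02 small, 0.15 moderate and 0.35 large. These are general statistical convention and are not given in the article. A value of 0.6 is not moderate on that scale. The larger the assumed effect, the smaller the required sample, so a mislabelled effect makes a small sample look sufficient.

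Aim 1 results are to inform the topics and agendas of the Aim 2 co-design sessions. A reader told that the survey is adequately powered could give a non-significant association more weight than it can bear.

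**Working it through.** **Inputs.** From Aim 1: sample size: effect 0.6, three predictors, alpha 0.05, N = 29, target 30 or more. From Aim 1: setting and sample: N = 50. From Table 1: models with two or three predictors. Assumed, because not stated: 0.6 is f-squared; power of 80%, 90% or 95%.

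**Formulas.** f² = R²/(1 − R²), so R² = f²/(1 + f²). For the overall (omnibus) test with p predictors, power = P(F′ > F crit), where F′ is noncentral F with df1 = p, df2 = N − p − 1 and noncentrality λ = f²·N. For one coefficient in a three-predictor model, df1 = 1, df2 = N − 4 and λ = partial f²·N, which is the two-sided t test.

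**Step 1: reproduce 29.** At f² = 0.6, the required N for 80/90/95% power is:
- three predictors, overall test: 23 / 28 / 33
- two predictors, overall test: 20 / 25 / 29
- single coefficient: 16 / 20 / 24

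At N = 29 with three predictors, λ = 0.6 × 29 = 17.4, df = 3 and 25, F crit = 2.99, and power = 91.4%. The stated 29 is thus close to 90% power with three predictors, and exact at 95% with two. The arithmetic is roughly sound for f² = 0.6.

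**Step 2: what 0.6 means.** R² = 0.6/1.6 = 0.375, and 0.6/0.15 = 4 times the moderate benchmark.

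**Step 3: other readings of 0.6** (three-predictor overall test).
- Multiple R = 0.6: f² = 0.36/0.64 = 0.5625; N = 24 at 80%, 30 at 90%. Above large.
- f = 0.6: f² = 0.36; N = 35 at 80%, 44 at 90%. Just above large.
- R² = 0.6: f² = 0.6/0.4 = 1.5; N = 12 at 80%, 15 at 90%. Far above large.
- Standardised difference d = 0.6, with two equal groups: r = 0.6/√(0.36 + 4) = 0.287, f² = 0.09. The label could stand here, but N = 126 is needed for 80% power.

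None of these makes 29 adequate for a moderate effect.

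**Step 4: power at f² = 0.15.** For the three-predictor overall test, λ = 0.15 × 29 = 4.35, 0.15 × 30 = 4.5 and 0.15 × 50 = 7.5.

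| Test | N = 29 | N = 30 | N = 50 | N for 80% |
|---|---|---|---|---|
| Overall, three predictors | 33.6% | 34.9% | 58.2% | 77 |
| Overall, two predictors | 40.4% | 41.8% | 65.8% | 68 |
| Single coefficient | 51.8% | 53.3% | 76.5% | 55 |

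**Step 5: detectable f² at 80% power, three-predictor model.**

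| Test | N = 30 | N = 50 |
|---|---|---|
| Overall | 0.42 (R² = 0.42/1.42 = 0.30) | 0.24 (R² = 0.24/1.24 = 0.19) |
| Single coefficient | 0.28 (partial R² = 0.28/1.28 = 0.22) | 0.16 (partial R² = 0.16/1.16 = 0.14) |

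**The case against.** The strongest reply is that the effect metric is unstated, so calling 0.6 an f-squared is an inference, and three predictors never give exactly 29 at the usual power levels. That is true and should be said. It does not rescue the power claim, because the readings as f, R and R-squared are also large or larger, and the d reading makes 29 far too few.

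A reader might go further than the document supports in four ways.

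- **Quoting 35% as the power of Aim 1.** That is the three-predictor overall test at about 30 participants. Seven of the ten Table 1 models have two predictors, and most of the stated purposes concern one exposure adjusted for sex, for which the single-coefficient figure is at least as natural.
- **Concluding that the survey can detect only very strong associations.** For a single coefficient the detectable f-squared is 0.28 at 30, which is below large, and 0.16 at 50, which is close to moderate.
- **Calling the reasoning reversed.** The low-power concern is the reason given for choosing a moderate effect over a large one, and that direction is correct. Avoiding a large effect is tied to feasibility scope. The fault is that 0.6 does not match its label.
- **Inferring that non-significant results will be used to drop co-design topics.** The article says only that results inform topics and agendas and that survey results are shared with co-designers.

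It is also fair that Aim 1 is an exploratory needs assessment, for which a small sample is defensible. What cannot be defended is describing it as adequately powered.

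**Conclusion.** The point holds. On the f-squared reading, 0.6 is above the conventional large value, so the label moderate and the statement "A decision was made to avoid selecting a large effect size" do not fit the number used. The claim of adequate power is not supported for a moderate effect: power is 34-53% at 29 to 30 participants and 58-76.5% at 50, depending on the test. Every case is below 80%.

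This rests on the conventional benchmarks, on alpha 0.05 without multiplicity adjustment, and on f-squared as the assumed metric, which is supported by its approximate reproduction of 29.

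It should be fixed but is not critical. Aim 1 is preparatory, and the Aim 3 feasibility outcomes and their target of 50 rest on separate reasoning.

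**What to change.** Change the wording of Aim 1: sample size; no added enrolment is needed.

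1. Name the effect metric and the numerical power level behind 29.
2. Remove the label moderate, the statement that a large effect was avoided, and the claim of being powered for meaningful effects.
3. State what the sample can detect. For example: with three predictors and 80% power at alpha 0.05, the detectable f-squared is about 0.42 for the overall test and 0.28 for a single coefficient with 30 participants, and about 0.24 and 0.16 with 50.
4. Reconcile the target of 30 or more with the 50 in Aim 1: setting and sample.
5. Add that non-significant Aim 1 associations will be interpreted as inconclusive, with the confidence intervals shown.

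The cost is a less favourable statement of power.
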